### Safety and adverse event outcomes

Both clonidine and pentoxifylline have a history of safe systemic use in humans, and there is evidence that topical application of these agents produces extremely low to undetectable plasma levels [27]. As no negative effects were observed in animals or adverse effects in our trial in healthy volunteers, we do not anticipate any adverse side-effects with our topical treatment [25, 28].

According to the FDA, rare events in patients taking pentoxifylline (although not established as caused by the drug) include anaphylactic reactions [32]. Subjects will be asked to immediately report any signs of anaphylaxis (itchy rash, lip or throat swelling) to the study coordinator, who will instruct the patient to go immediately to a hospital emergency room.

Risks involved in taking clonidine orally are dizziness, light-headedness, drowsiness, tiredness, and vision problems, which are caused by a decrease in blood pressure [33]. Patients will be asked to immediately report any of these symptoms to the study coordinator, who will instruct the patient to see the study physician, who will perform a medical evaluation, including assessment of blood pressure. If any subject’s systolic pressure is found to be below 80 mmHg, they will be asked to stop the treatments and will be removed from the study. Abrupt discontinuation of clonidine can occasionally result in a withdraw syndrome, characterized by a rebound increase in blood pressure and other symptoms and signs of sympathetic activity like restlessness, increased heart rate, and increased irritability [34]. This usually occurs after cessation of large oral doses and in some instances after transdermal treatment. There is minimal risk for this syndrome with our study drug, as the dose of clonidine used is much lower than oral or transdermal preparations. Patients will be asked to report to the study coordinator if any of these symptoms occur during the washout period of the study and the few days following completion of the study. Clinical evaluation and appropriate medical care will accordingly be provided.

All adverse events will be tabulated, summarized, and reviewed by the study physician. Serious adverse drug reactions, i.e., reactions causing hospitalization; persistent or significant disability; that is life-threatening or resulting in death, will be immediately reported to the study sponsor who is the primary investigator and the research ethics coordinator for the study site. Serious adverse drug reaction reporting will follow International Council for Harmonization (ICH) guidelines.

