### Interventions

All participants will be randomized to treatment with either active drug or placebo in one of the two 2-week-long treatment blocks of the study. The active drug is an anhydrous topical solution containing 0.1% (W/V) clonidine and 5% (W/V) pentoxifylline. The placebo is a blank version of the anhydrous solution with constituents identical with the active drug except omitting the therapeutic agents, i.e., clonidine and pentoxifylline. The stability of the topical solutions at room temperature has been ascertained with mass spectrometric studies done upon the request of Health Canada. The exact composition of the active drug and placebo is as outlined in Table 2.

**Table 2 Tab2:** Composition of 100 ml of the active drug topical solution with 0.1% (W/V) clonidine and 5% (W/V) pentoxifylline

**Solid ingredients**		**Amount (g)**
1	Clonidine	0.1
2	Pentoxifylline	5.0
**Liquid ingredients**		**Amount (ml)**
3	Anhydrous ethanol	6.2
4	Polyethylene glycol 400	18.9
5	Oleyl alcohol	50.8
6	Propylene glycol	18.9

Both the active drug and placebo solutions are colorless and will be packaged in identical Topi-Pump® dose-metered applicators that dispense 1 ml of topical solution with each pump. Participants will be instructed to apply one pump or 1 ml of the topical solution three times daily on an eight-hourly basis. They will also be asked to return the emptied pumps after use so adherence to treatment can be monitored.

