### Randomization and blinding

Randomization for treatment order (placebo–active drug/active drug–placebo) is performed by a coin flip done by a research coordinator assigned for this task who is not involved in patient interaction and outcome assessment. The same coordinator also ensures blinding by assigning a three-digit number code, from a computer-generated random list, to the Topi-Pumps used in each treatment block. The list of number codes and the identity of their corresponding treatment is only shared with the compounding pharmacy. The blinding applies to the patient, the study coordinator performing patient assessments, and the dispensing pharmacy.

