### Endpoints and post-trial care

Eligible patients are expected to have stable disease with no alteration to their treatment regimen in the 5 weeks preceding enrollment. If a patient develops uncontrolled pain with a clinical indication for a new treatment during the study period, the participation of the patient in the trial will be discontinued and the new treatment commenced. If any subject’s systolic pressure is found to drop below 80 mmHg during any section of the trial, they will be asked to stop the treatments and they will be removed from the study. Finally, in the event of an anaphylactic reaction to any of the topical treatments used in the study, the patient’s participation in the study will immediately be terminated. In both instances, the coordinator performing the randomization will send the study physician the information required to unblind him to the study drug the patient was taking so the information can be transferred to the medical team that will care for the patient.

Patients will be instructed to contact the study coordinator and/or physician if symptoms of clonidine withdrawal occur during washout or the week following completion of the study. In such an event, the study physician will perform a clinical evaluation of the patient and appropriate medical care will be provided. Unblinding and termination of participation in the study will depend on the study physician’s assessment of the patient’s clinical status.

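### The written pathway for signs of anaphylaxis puts a report to the study coordinator ahead of emergency care, although every listed sign leads to the same destination

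*Protocol article*

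**What the plan says.** The pathway is in the protocol article under Safety and adverse event outcomes. The patient's step is: "Subjects will be asked to immediately report any signs of anaphylaxis (itchy rash, lip or throat swelling) to the study coordinator". The coordinator's step follows in the same sentence: "who will instruct the patient to go immediately to a hospital emergency room". No condition, triage or alternative is attached to that instruction.

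Three other places describe what the study does with the information:

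- Later in the same section, serious adverse drug reactions "will be immediately reported to the study sponsor who is the primary investigator", and to the research ethics coordinator for the site.
- Endpoints and post-trial care ends the patient's participation "in the event of an anaphylactic reaction to any of the topical treatments used in the study". For unblinding, "the coordinator performing the randomization will send the study physician the information required to unblind him", "so the information can be transferred to the medical team that will care for the patient".
- Randomization and blinding gives the allocation task to "a research coordinator assigned for this task who is not involved in patient interaction and outcome assessment".

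Interventions has participants "apply one pump or 1 ml of the topical solution three times daily on an eight-hourly basis", and Outcomes has pain recorded at home.

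**The concern.** Throat or lip swelling can be an emergency in which time matters. The sponsor has already decided that any of the listed signs warrants an emergency room. A contact placed before that decision takes effect does not alter where the patient is sent, and it takes some time if the patient treats it as the first step.

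Dosing is eight-hourly and the patient applies the solution, so signs may well begin when no study staff are present and possibly outside working hours. What is at stake is the time to emergency care in an unlikely but potentially grave event. The step order has no bearing on the treatment comparison, the sample size or the error rate.

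**Working it through.** There is no stated figure to reproduce and no arithmetic applies. The check is a reading of the sections against one another.

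**1. Order of steps.** The safety section gives: sign appears, patient reports to the coordinator, coordinator instructs, patient goes to the emergency room. The only action given to the patient before the instruction is the report. No section shown tells the patient to go directly or to call emergency services first.

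**2. Does the report affect the destination?** Three signs are listed (itchy rash, lip swelling, throat swelling) and one instruction covers all of them. The coordinator makes no choice, so the destination is known before the contact is made.

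**3. Comparison within the same section.** For dizziness, light-headedness, drowsiness, tiredness and vision problems, the same coordinator-first route is used, but it sends the patient to the study physician for a medical evaluation that includes blood pressure. There the contact gives access to a service inside the study team. For signs of anaphylaxis the same route leads to a service outside the study that the patient can reach unaided.

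**4. Do the other uses of the report require it to come first?**

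- *Reporting of serious reactions* runs from the study to the sponsor and the ethics coordinator. It can start while the patient travels or is treated.
- *Termination of participation* is a study action and can also follow the patient's departure.
- *Unblinding* passes from the randomizing coordinator to the study physician and then to the treating team. The randomizing coordinator has no patient contact, so the coordinator whom the patient reaches is not the one assigned to release the code. This process too can run in parallel with emergency care.

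All three need prompt notice. None needs notice before the patient leaves.

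**5. What the document says about risk.** The safety section describes anaphylactic reactions as rare in patients taking pentoxifylline and not established as caused by it. It cites extremely low to undetectable plasma levels after topical use, and it reports no adverse effects in the healthy-volunteer trial. The eligibility criteria exclude patients with known allergy to either drug. No event rate or contact time is given, so neither an expected number of events nor a delay can be calculated. Counting one contact before care under the present wording and none under a revised one describes the sentence, not the size of the harm.

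**The case against.** The strongest objection is that any harm depends on what patients are actually told. The consent form and instruction sheet are not shown, the article condenses a fuller protocol, and staff receive training in study procedures that is also not shown. A direct-to-emergency instruction may exist in any of these. This stands as a limit on the size of the concern. It does not remove it, because the article does more than stay silent: it sets out a sequence and describes it as what subjects will be asked to do.

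A second objection is that the sentence is a reporting duty with a fixed response, not a gate. Both steps are described as immediate. A reader might infer that patients must wait for the coordinator, or need permission, before seeking care. The text does not say so, and nothing in it forbids going directly.

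A third objection concerns the value of the contact. A reader might infer that the call is useless before emergency care and can do nothing but cost time. That goes too far. A patient with rash alone, using a solution applied to the skin, might stay at home unless prompted, and the call could be what brings that patient in. This stands. It supports keeping the notification and giving the prompt in advance, but it does not require the call to come first for lip or throat swelling.

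Finally, the documents point to low risk, and no delay can be quantified. This also stands and determines the severity.

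**Conclusion.** The point holds in a limited form. As written, the pathway places a report to the coordinator before emergency care for signs whose destination is already fixed. If followed in that order, it can delay care without need. The conclusion rests on the sequence stated in the article and on the assumption that patients are instructed in that sequence, which cannot be verified here.

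Severity is minor and the matter is one of patient safety only. The document gives no basis for a number of patients affected or a length of delay.

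A reader might also infer that dosing must stop at the first sign. That does not follow from the order of steps. It is a separate, optional precaution with its own cost, described under the fix.

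**What to change.** Reword the sentence in Safety and adverse event outcomes along these lines: subjects are told in advance that, at any itchy rash or lip or throat swelling, they should go directly to a hospital emergency room or call emergency services; they should inform the study coordinator as soon as possible on the way, on arrival or through someone else. State that this notice starts serious-reaction reporting, termination and unblinding for the treating team. Leave the provisions for those three steps unchanged. If the patient instruction sheet follows the present order, change it to match; if it already sends patients directly, only the protocol sentence needs aligning.

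**Cost.** One sentence, and possibly one line of the patient sheet, submitted to the research ethics board by the route given under Trial status. No extra staff are needed. The written rule already sends every patient with these signs to an emergency room, so the set of signs that trigger referral is unchanged. Actual attendance could still shift, because an advance instruction replaces the coordinator's prompt. The main drawback is that the study may hear of the event slightly later, so unblinding may start slightly later. Notice on the way or through another person limits this.

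**Optional addition.** The sponsor may also ask subjects to withhold further doses until medically assessed. With three applications a day, the cost is up to three missed doses for each day of waiting. In a patient whose sign proves benign, this could touch the diary data, in particular the second-week scores used in the primary comparison. It should be decided on its own merits.

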### Endpoints and post-trial care

Eligible patients are expected to have stable disease with no alteration to their treatment regimen in the 5 weeks preceding enrollment. If a patient develops uncontrolled pain with a clinical indication for a new treatment during the study period, the participation of the patient in the trial will be discontinued and the new treatment commenced. If any subject’s systolic pressure is found to drop below 80 mmHg during any section of the trial, they will be asked to stop the treatments and they will be removed from the study. Finally, in the event of an anaphylactic reaction to any of the topical treatments used in the study, the patient’s participation in the study will immediately be terminated. In both instances, the coordinator performing the randomization will send the study physician the information required to unblind him to the study drug the patient was taking so the information can be transferred to the medical team that will care for the patient.

Patients will be instructed to contact the study coordinator and/or physician if symptoms of clonidine withdrawal occur during washout or the week following completion of the study. In such an event, the study physician will perform a clinical evaluation of the patient and appropriate medical care will be provided. Unblinding and termination of participation in the study will depend on the study physician’s assessment of the patient’s clinical status.

### Compensation

Participants will receive reimbursement of travel expenses up to a sum of 100 Canadian dollars. If participants fail to complete the study, the compensation they receive will be pro-rated amounts based on the duration of participation.

## Discussion

The peripheral neuropathic pain patient population is composed of a sizable number of patients that can benefit from avoiding the systemic anticonvulsants and antidepressants that are first-line treatments of the condition [3–5]. Given their typically older age and comorbid conditions, these patients are at greater risk of developing adverse events from these recommended systemic treatments [4, 5]. This clinical study is a required step in developing a locally-administered, potentially effective and tolerable analgesic alternative for the treatment of peripheral neuropathic pain.

As a phase II clinical trial, this study is a proof-of-concept step to evaluate the potential efficacy and safety of the topical combination of clonidine and pentoxifylline in peripheral neuropathic pain [35]. To optimize the detection of hypothesized analgesic effects, the selection of the study population is restricted to a specific subgroup of neuropathic pain patients with an uncomplicated medical profile.

The cross-over design of the study was another step taken to increase the efficiency of the initial screening of the formulation’s analgesic effects. The design allows the use of a relatively small number of patients by minimizing between-subject data variability thereby reserving resources and time [35, 36]. We believe the 2-week duration of treatment is long enough to reveal the alleviation of neuropathic pain symptoms achieved. At the same time, the treatment is set to be brief enough to avoid long-term effects that can potentially change the underlying pathology preventing effective washout. The 1-week-long washout period is based on evidence obtained from the pharmacokinetics of constituent drugs and the length of analgesic effects measured from neuropathic rodent models and healthy volunteers treated with the formulation [25, 28, 33, 37]. It is expected that this time frame is sufficient in duration and carry-over effects are unlikely to occur.

Clinical trials with cross-over designs with relatively few patients have been used to successfully detect the efficacy of analgesics in painful diabetic neuropathy, post-herpetic neuralgia, and post-traumatic neuropathic pain [38–40]. The cross-over design assures the patients that treatment with both placebo and the active drug will occur prompting them to think more objectively about their pain levels in each period. This has resulted in significantly lower placebo group response rates in cross-over trials as compared to parallel-group trials, as reported in a meta-analysis of neuropathic pain trials [41].

With randomization and blinding, we have tried to maintain the internal validity of the study. Outcome measures were chosen to pointedly assess the analgesic efficacy and solely focus on discovering the degree of relief from spontaneous and evoked pain [42]. A broader investigation of physical-functional outcome and overall improvement of quality of life is undoubtedly necessary, but will be reserved for subsequent study phases that will be performed after initial proof of efficacy has been obtained for the formulation [43].

The outcome measures used as comparators in this study are kept the same as what has been used in the healthy volunteer human-study performed with the topical combination [28]. The measures comprehensively assess both spontaneous and evoked pain. The VAS ratings employed for assessments of daily levels of spontaneous pain and the degree of dynamic mechanical allodynia have a proven high degree of resolution and sensitivity in clinical pain research [44].

To the best of our knowledge, this study is the first randomized, double-blind, and placebo-controlled clinical trial to assess the analgesic efficacy of the topical combination of clonidine and pentoxifylline in neuropathic pain. Topical clonidine on its own has been investigated in this manner for the treatment of painful diabetic neuropathy and a positive outcome has been reported [27]. In complex regional pain syndrome, there have been clinical case reports of analgesic benefits achieved with the use of bare topical clonidine, and topical clonidine in combination with pentoxifylline, ketamine, and dimethyl sulfoxide [26, 45]. However, the level of evidence from these studies does not allow a reliable conclusion to be drawn on the therapeutic benefit of the topical treatments.

Lastly, relevant clinical data is required to affirm the abundant preclinical evidence on the role of poor nerve oxygenation and blood supply in the genesis of peripheral neuropathic pain [10, 25, 46–48]. This study is a means of achieving that, above and beyond presenting a specific drug formulation with potential efficacy for the treatment of peripheral neuropathic pain. The results can furthermore potentially promote the investigation of other vasodilatory agents for analgesic effects, building a new collection of safe and effective drugs for the treatment of peripheral neuropathic pain.

### Trial status

The study is currently actively recruiting and enrolling eligible participants. Recruitment started in January 2019 and the study is forecasted to be completed by January 2021. This is protocol version 5, dated June 2018. MUHC-REB identification number: TTNP 2018-3906. If significant changes requiring the modification of this protocol are required, the changes will be submitted for approval to the MUHC-REB through its web-based platform Nagano.

## Data Availability

There are no plans to publicly share the raw data or materials used during this clinical trial. There are plans to communicate the results of the analyzed data through conference presentations and publications in relevant journals.

## Abbreviations

clon: Clonidine
DMA: Dynamic mechanical allodynia
FDA: US Food and Drug Administration
GCP: Good Clinical Practice
IHC: International Council for Harmonization
MUHC: McGill University Health Centre
NO: Nitric oxide
pentox: Pentoxifylline
PHA: Punctate Hyperalgesia
REB: Research ethics board
VAS: Visual analog scale
W/V: Weight/volume
